**Ethics and dissemination:**

The study will bring new knowledge on the risk of developing obesity, cardiometabolic morbidity and mortality following treatment for hyperthyroidism to inform clinical practice and public health policies. The results will be disseminated via open-access peer-reviewed publications and directly to the patients and public groups (Independent Scientific Advisory Committee protocol approval #20_000185).

Strengths and limitations of this studyRich data from a large sample allowing for pre-exposure history and long follow-up, spanning across primary and secondary care.Contextualisation of post-treatment obesity prevalence by comparison with the general population adjusted for sex and age.A broad range of patient-relevant cardiometabolic outcomes will be evaluated.Large real-world observational study of treatment options not amenable to randomised clinical trials.The study’s main limitations are related to the intrinsic nature of the real-world data, such as the secondary use of data or the presence of missing data.

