## Introduction

Hyperthyroidism is a common condition affecting 3% of women and 0.3% of men in the UK.^1^ Common clinical features indicating hyperthyroidism include weight loss, heat intolerance, tremor, palpitations and anxiety.^2^ Treatment is critical to minimise complications including atrial fibrillation and stroke that contribute to the observed 20% increase in mortality.^3^

There are three treatment options: antithyroid drugs (ATDs), radioactive iodine (I-131, radioiodine) or surgical, either as a total or hemithyroidectomy. ATDs are associated with a high rate of relapse (30%–70%),^4^ while treatment with radioiodine or thyroidectomy leads to the development of hypothyroidism, requiring lifelong levothyroxine replacement, which is seen in 80% of patients administered radioiodine and up to 100% undergoing thyroidectomy. Guidance recommends discussion of all three options with the patient.^5 6^ There is insufficient evidence to recommend one treatment over the others, although some studies indicate differences in cardiac events and mortality between the treatment modalities.^7 8^

Weight gain following various treatments for hyperthyroidism has been described.^9 10^ Clinicians commonly assume that the observed weight gain is a simple regain of weight lost prior to the initiation of treatment. However, an analysis of 1373 patients with hyperthyroidism has demonstrated a higher prevalence of obesity at 3 years of follow-up when compared with the age-matched and sex-matched background population (37% vs 26% in men, p<0.001; 32% vs 26% in women, p<0.001).^11^ These findings suggest excess weight gain beyond patients’ premorbid weight (weight overshoot). Additionally, the study showed significant differences in final weight gain compared with baseline between those treated with ATDs (5.4 kg, 95% CI 4.8 to 6.0) and those who received radioiodine but did not develop hypothyroidism (5.1 kg, 95% CI 4.3 to 6.1) when compared with those treated with radioiodine who developed subsequent hypothyroidism (7.1 kg, 95% CI 6.6 to 7.7). The extent of weight change in patients treated with thyroidectomy was not evaluated.

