### Data sources

CPRD collects and anonymises patient electronic health record data from a network of general practitioner (GP) practices across the UK.^19^ Although the records in the database cover all four UK countries, HES-linkable records are limited to those from England only. Two HES datasets will be used: HES outpatient and HES admitted patient care. Linkage to HES databases is required to obtain the data, which may be missing from the GP records on non-medical treatment for hyperthyroidism (radioactive iodine and thyroidectomy). Additionally, data on MACEs will also be sourced from HES, as such events are typically being treated in the hospital setting.

Linkage to social data is required to adjust the analysis for socioeconomic status, which is a known risk factor for obesity and increased mortality. This will be obtained as the Index of Multiple Deprivation (IMD). Linkage to Office of National Statistics data is required to get access to the date of death and cause of death. Prevalence of post-treatment obesity will be compared with the background population sourced from Health Survey for England, a yearly survey monitoring trends in the nation’s health and care.

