### Population

Adult patients (≥18 years) who were for the first time diagnosed with hyperthyroidism (the list of codes in online supplemental appendix) between 1 January 1996 and 31 December 2015 will be eligible for inclusion. To minimise missed cases, the diagnosis will be additionally identified by a prescription of carbimazole or propylthiouracil, which are ATDs indicated only for treatment of hyperthyroidism. A minimum of 12 months of data must be available before the date of diagnosis and after the index date. CPRD records need to be classified as acceptable research quality.

10.1136/bmjopen-2021-055219.supp1Supplementary data

Exclusion criteria encompass ATD treatment of duration shorter than 6 months as the only treatment, that is, with no radioactive iodine or thyroidectomy followed. This is to avoid contamination by misdiagnosis or spontaneously resolving thyroiditis. Patients treated with both definitive treatment methods, that is, radioiodine and thyroidectomy, will also be excluded. However, ATD treatment followed by either radioiodine or thyroidectomy (one of the definitive treatments) is considered a pretreatment and does not constitute an exclusion criterion.

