#### Prevalence of obesity

Post-treatment obesity in patients will be defined as ≥30 kg/m^2^, in line with the WHO definition,^26^ or identified from the Read codes when quantitative values are not available. The prevalence of obesity will be assessed in the entire cohort and stratified by the treatment group.

The post-treatment BMI will be compared with those in the background population (Health Survey for England). Two measures of effect will be investigated: (1) difference in overall BMI (kg/m^2^) and (2) difference in proportions of obesity. The effects will be tested with linear regression and logistic regression, respectively, in reference to the background population. The analyses will be adjusted for age and stratified by sex. Only complete case analysis will be conducted.

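### The comparison of post-treatment obesity with the Health Survey for England omits calendar year, so an obesity trend may inflate or hide the excess if the two sources cover different years

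*Protocol article*

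**What the plan says.** All references are to the Protocol article.

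- **Models.** Under Prevalence of obesity, the BMI difference is tested by linear regression and the obesity proportion by logistic regression, with the background population as reference. The adjustment and the missing-data rule are fixed: "The analyses will be adjusted for age and stratified by sex. Only complete case analysis will be conducted". The strengths and limitations list repeats the adjustment as a merit: "Contextualisation of post-treatment obesity prevalence by comparison with the general population adjusted for sex and age".
- **Comparator.** Data sources says that the background population is "sourced from Health Survey for England, a yearly survey monitoring trends in the nation’s health and care". The survey years to be used are not given.
- **Patients.** Population admits adults first diagnosed "between 1 January 1996 and 31 December 2015 will be eligible for inclusion". Under Natural history of weight changes, every weight recorded later than 3 months after the last treatment date counts as post-treatment, with no upper limit.
- **Covariates.** The Confounding section and its Table 2 include time since diagnosis, but not calendar year.
- **Missing data.** For the obesity comparison: "Only complete case analysis will be conducted". Obesity status may also be "or identified from the Read codes when quantitative values are not available". Under Natural history of weight changes, the plan expects a fairly high share of missing weights, assumes that they are missing at random given covariates, and imputes them.
- **Size of effect in earlier work.** The Introduction cites an earlier cohort with obesity prevalence at 3 years, patients against background, of "37% vs 26% in men, p<0.001; 32% vs 26% in women, p<0.001".

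**The concern.** The stated models treat two people of the same age and sex as exchangeable even if one was weighed in 1998 and the other in 2015. Age cannot stand in for calendar year. If background obesity changes over time and the HSE years used do not mirror the years of the patients' BMI records, being a patient is confounded with calendar time. The group coefficient then mixes any true excess with the trend. Earlier HSE years would inflate the excess under a rising trend, and later ones would hide it.

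The comparison belongs to the primary objective and the primary outcome, and the gaps reported in earlier work are modest. A bias of a few points would matter.

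A second, smaller issue is that the plan expects many missing weights and imputes them for the trajectory analysis, but rules out anything beyond complete cases here. If being weighed depends on weight, patients with a recorded BMI may not represent all treated patients.

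**Working it through.** The plan gives no sample size, power or effect figure for this comparison, so there is nothing to reproduce. The check asks how large the bias could be.

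**Inputs from the article.** Cited gap in men: 37 − 26 = 11 points. Cited gap in women: 32 − 26 = 6 points. As odds ratios:
- men: (0.37/0.63)/(0.26/0.74) = 1.67
- women: (0.32/0.68)/(0.26/0.74) = 1.34

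**Assumptions, not in the article.** Background obesity rises by 0.2 to 0.5 percentage points per year. Mean measurement years in the two sources differ by 5.

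**Calendar bias.** Bias in prevalence difference ≈ slope × gap in mean year.

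| Slope (points/year) | Gap (years) | Bias (points) | Share of 6 (women) | Share of 11 (men) |
|---|---|---|---|---|
| 0.2 | 5 | 1.0 | 17% | 9% |
| 0.5 | 5 | 2.5 | 42% | 23% |
| any | 0 | 0 | 0% | 0% |

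**Check by simulation with no true excess.** Assumptions: one sex; 200,000 records per group; 26% prevalence in 2008; patient weights spread evenly over 1998–2019; the same age distribution in both groups; linear slopes of 0.3, 0.5 and 0.7 points per year. The logistic model with group and age is set against the same model with year added.

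| HSE years assumed | Spurious difference (points) | Odds ratio, age only | Odds ratio, age and year |
|---|---|---|---|
| 1998–2019 (matched) | −0.2 to +0.1 | 0.99 to 1.01 | 0.99 to 1.01 |
| 1996–2005 (earlier) | +2.5 to +5.5 | 1.14 to 1.36 | 0.99 to 1.00 |
| 2015–2019 (later) | −2.6 to −5.6 | 0.88 to 0.76 | 0.98 to 1.01 |

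The slopes and year gaps here are wider than in the first table. The simulation shows that the bias takes either sign, vanishes when years match, and is removed by a year term. At its upper end the false odds ratio (1.36) is about the size of the one implied by the women's cited gap (1.34).

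**Selective weighing (illustration only).** Observed prevalence = p × P(weighed | obese) / P(weighed), with p = 26%. The share weighed and the odds ratio for being weighed if obese are assumed.

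| Share weighed | Odds ratio 1.25 | Odds ratio 1.5 | Odds ratio 2 |
|---|---|---|---|
| 50% | +2.1 | +3.9 | +6.6 |
| 70% | +1.3 | +2.2 | +3.7 |
| 90% | +0.4 | +0.7 | +1.1 |

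Entries are points above 26%. An odds ratio below 1 would reverse the sign. The article supports neither a direction nor a size.

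**The case against.** The strongest reply is that the article nowhere says that HSE years will be pooled out of line with the BMI dates. Choosing survey years is a detail that a full protocol may hold, and year matching would sit beside adjustment for age and sex without contradiction. This stands in so far as the bias is conditional and not certain. It does not dispose of the point: the article states its adjustment set twice, and year is in neither statement.

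Three stronger readings are tempting, and the article does not support them.

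- **That the trend would be mistaken for an effect of treatment.** The contrast is treated patients against the population. Differences between treatments in weight are estimated in a separate model, with antithyroid drugs as reference.
- **That the whole case for weight overshoot rests on this comparison.** The trajectory analysis also follows each patient from premorbid to post-treatment weight.
- **That selective weighing is shown to bias the result.** The article expects missing weights but gives no pattern by weight. Read codes recover some obesity status, though not the BMI value that the linear model needs.

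The contrast with the trajectory analysis can also be overdrawn. That analysis itself admits only patients with a weight record in all three phases, so its imputations cannot recover patients with no post-treatment record. Finally, the 6- and 11-point gaps come from an earlier cohort, and the plan does not adopt them as its expected effect. They serve only as a yardstick. A single fixed window for post-treatment BMI would be a design preference, not the correction of an error.

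**Conclusion.** The point holds in conditional form. As written, the models for part of the primary outcome omit calendar year, and nothing in the article aligns a yearly survey with BMI records that follow 20 years of diagnoses. If the year distributions differ, the excess over the population may be over- or understated. The 1.0 to 2.5 point figure rests entirely on the assumed slope and 5-year mismatch. The upper share, 42%, is the extreme of that range and applies to women only.

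The complete-case rule is a secondary weakness. It sits poorly with the missingness that the plan itself expects, but its effect cannot be sized from the article. The change should be made before analysis; nothing here shows that the comparison is invalid.

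**What to change.** 1. Match each post-treatment BMI to the HSE survey of the same calendar year. Alternatively, add year of measurement, as categories or a spline, to both the linear and the logistic model. State which HSE years are used. The year term needs years that overlap between the sources; without overlap it extrapolates.
2. Keep the complete-case analysis and add one sensitivity analysis for missing BMI. Either weight by the inverse probability of having a post-treatment measurement, or impute with a model built for all eligible patients. Do not reuse the imputations from the three-phase weight model. Say that this analysis still relies on missing at random.
3. Amend the strengths statement to include calendar year.

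The cost is one covariate, or a matching step, and one extra analysis run. HSE is already yearly, so no new source is needed.

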#### Primary objective

The primary aim of this study was to assess the effect of type of treatment on weight changes during and after therapy for hyperthyroidism. The post-treatment prevalence of obesity will also be evaluated and compared with that of the general population.

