### Confounding

Based on the literature and clinical experience, we identified a number of confounders affecting both the exposure and the outcomes of our study. The modelled outcomes will be adjusted for baseline data (sex, age, IMD quartiles, smoking status and comorbidities) and time-varying covariates (thyroid function, cumulative time on the medical treatment, time since diagnosis, levothyroxine replacement, pregnancy and diagnosis of cancer). Table 2 presents the details of how covariates are defined and handled. Figure 1 depicts the directed acyclic graphs representing the relationship between the covariates. We will explore the relationships between the potential confounders and both exposures and outcomes independently in order to establish their potential role in this particular dataset.

**Table 2 T2:** Definitions of study covariates

Variable	Definition
Aetiology of hyperthyroidism	Identified based on Read codes and categorised in (1) Graves’ disease, (2) toxic nodular goitre and (3) undefined. The undefined category will consist of unspecified diagnosis and missing aetiology data.
Age	Age at index date
Baseline fT4	The highest measurement between 3 months prior to diagnosis and the index date
BMI	Normal (or underweight) <25 kg/m^2^, overweight 25–30 kg/m^2^ and obese ≥30 kg/m^2^; additionally, BMI status will be deduced from the Read code
Cancer diagnosis	Switch-type binary variable assuming lifelong status of cancer comorbidity
Frequency of GP visits	Time-varying variable of number of GP visits in a unit of time
IMD	IMD will be stratified into quintiles.
Levothyroxine (LT4) replacement	Switch-type binary variable assuming lifelong LT4 administration following development of hypothyroidism in radioiodine and thyroidectomy treatment groups
Pregnancy	Time-varying binary variable recording pregnancy
Pretreatment ATD	Cumulative time on ATD between diagnosis and the index date
Sex	Binary variable
Smoking status	As recorded at the index date, last observation carried forward if not available at the index date
TSH	Serial TSH, log-transformed for the analysis
Time since diagnosis	Time-varying variable measuring cumulative time since diagnosis

ATD, antithyroid drug; BMI, body mass index; GP, general practitioner; IMD, Index of Multiple Deprivation; TSH, thyroid-stimulating hormone.

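### The obesity comparison with the general population adjusts only for age and sex, although deprivation data are linked because deprivation predicts obesity; a second model with deprivation and smoking would be a cheap safeguard

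*Protocol article*

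**What the plan says.** The comparison belongs to the primary objective: "The post-treatment prevalence of obesity will also be evaluated and compared with that of the general population". Under Prevalence of obesity, the article names two measures, the difference in BMI and the difference in the proportion obese, and says: "The effects will be tested with linear regression and logistic regression, respectively, in reference to the background population". The adjustment set follows: "The analyses will be adjusted for age and stratified by sex". Only complete cases are used. The strengths list in the abstract agrees: "Contextualisation of post-treatment obesity prevalence by comparison with the general population adjusted for sex and age".

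Under Data sources, the reason for obtaining the Index of Multiple Deprivation (IMD) is: "Linkage to social data is required to adjust the analysis for socioeconomic status, which is a known risk factor for obesity and increased mortality". The Confounding section says: "The modelled outcomes will be adjusted for baseline data (sex, age, IMD quartiles, smoking status and comorbidities", and the same sentence goes on to time-varying covariates. IMD and smoking enter the propensity model for cardiometabolic outcomes and mortality. No section carries either of them into the comparison with the survey.

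The Introduction cites earlier obesity differences from the background population ("37% vs 26% in men, p<0.001; 32% vs 26% in women, p<0.001") and takes them to suggest weight gain beyond the premorbid level.

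**The concern.** The article itself identifies deprivation as a determinant of obesity and obtains the data to adjust for it. The one analysis that sets obesity in patients against the general population leaves it out, together with smoking.

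The cohort consists of treated patients in English practices with linkable hospital records who also have a usable post-treatment BMI. Nothing in the design makes their deprivation or smoking mix match that of a population survey. Splitting the patients by treatment group does not help, because each group is compared with the same survey.

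At stake is how a difference is interpreted. If it is read as overshoot after treatment, as the Introduction reads the earlier study, a difference in social mix would be counted as part of that overshoot or would offset it.

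**Working it through.** The article gives no sample size, power or significance level for this comparison, so there is no stated figure to reproduce. It gives no IMD or smoking distribution for either source. Apart from the cited 26% background obesity and the earlier differences, every input below is an assumption.

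**Deprivation.** Let the survey have 20% in each IMD quintile. Let obesity rise linearly by *g* from the least to the most deprived quintile. Let the cohort have *t* more in the most deprived and *t* less in the least deprived quintile, with half that shift in the adjacent quintiles. With no treatment effect,

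bias = Σ (cohort share − 0.20) × prevalence = *t* × *g* + (*t*/2) × (*g*/2) = 1.25 × *t* × *g*.

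Example: *g* = 15 points (20% to 35%) and shares of 16/18/20/22/24% (*t* = 0.04) give 0.04 × 15 + 0.02 × 7.5 = 0.75 points.

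| Gradient *g* | *t* = 2 points | *t* = 5 points | *t* = 10 points |
|---|---|---|---|
| 8 points | 0.20 | 0.50 | 1.00 |
| 10 points | 0.25 | 0.63 | 1.25 |
| 15 points | 0.38 | 0.94 | 1.88 |

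The range is about 0.2 to 1.9 points. A shallower 5-point gradient gives 0.13 to 0.63. If the cohort is less deprived than the survey, *t* changes sign and so does the bias.

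**Smoking.** Bias = (obesity difference, smokers minus non-smokers) × (difference in smoking prevalence). With ±3 to ±6 points and 5 to 15 points, this runs from ±0.15 (0.03 × 0.05) to ±0.9 points (0.06 × 0.15).

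**Chance that a bias alone reaches two-sided p<0.05.** Take 0.75 points at a prevalence of 27.5%, with equal numbers of patients and survey respondents: SE = √(2 × 0.275 × 0.725 / n), and rejection probability = Φ(0.75/SE − 1.96) + Φ(−0.75/SE − 1.96).

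| n per group | SE (points) | 0.75/SE | False-positive rate |
|---|---|---|---|
| 2,000 | 1.41 | 0.53 | 8% |
| 5,000 | 0.89 | 0.84 | 13% |
| 10,000 | 0.63 | 1.19 | 22% |

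On a 26% background with 10,000 per group, a spurious 1-point difference is significant with probability 0.36 and a 2-point difference with probability 0.89.

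**Scale.** The earlier differences were 37 − 26 = 11 points in men and 32 − 26 = 6 points in women.

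**The case against.** A comparison adjusted for age and sex is a legitimate description of how treated patients stand against the background population. The choice is disclosed, stated consistently in two places, and matches the age- and sex-matched comparison of the earlier study. Adjusting for deprivation and smoking answers a somewhat different question. Overshoot is also examined within patients, across the premorbid, treatment and post-treatment phases, and a fixed social difference from a survey does not enter that contrast. All of this stands, and it is why the age-sex model should be kept. It does not remove the risk in interpretation, because the Introduction draws overshoot from a population comparison of this kind.

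A reader might infer that the Confounding section contradicts the obesity section. The text does not support that. The Confounding section concerns "we identified a number of confounders affecting both the exposure and the outcomes of our study", and the article defines the exposure as the treatment. Its covariates include time since diagnosis and cumulative time on medical treatment, which a survey respondent cannot have. The list serves the comparison between treatments. Nor does Data sources promise IMD adjustment for this particular analysis.

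A reader might also infer that the omission inflates obesity after treatment. The documents do not show that the cohort differs from the survey at all, and a less deprived cohort would hide an excess.

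Finally, counting only the patients' sampling error (SE = √(0.275 × 0.725 / n)) gives false-positive rates of 12%, 22% and 39% at the same three sizes. Those overstate the problem, since the survey is itself a sample.

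**Conclusion.** The point holds as a modest weakness in the choice of adjustment. The bias is possible, not demonstrated, and its direction is open. It would be about 0.2 to 2 points for deprivation and under 1 point for smoking, which is unlikely alone to explain a difference of 6 to 11 points. It could produce or mask a small significant difference if the cohort is large. These sizes rest on the assumed obesity gradients, deprivation and smoking mixes, group sizes and an equal-sized survey. The change is a cheap improvement and not a condition for the analysis to be valid as description.

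**What to change.** Under Prevalence of obesity, keep the age-adjusted, sex-stratified linear and logistic models, which preserve comparability with the earlier study. Add a second linear and a second logistic model that also adjust for IMD quintile and smoking status, coded alike in the cohort and the survey. State that any reading of excess obesity as weight overshoot will rest on the fully adjusted result. The text under Confounding refers to IMD quartiles and Table 2 to quintiles, so the coding should be settled at the same time.

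This assumes that the survey data carry both measures, which the article does not say. If one is absent, adjust for the other, report the cohort's IMD and smoking distribution beside the comparison, and label the comparison descriptive.

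The cost is low: the study already derives both covariates for the patients. What remains is aligning the coding with the survey and a small loss of records with missing smoking or IMD under the complete-case rule.
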